## **8 CONDUCT OF STUDY**

### **8.1 Study Blinding and Randomization**

Subjects who fulfill the eligibility criteria and provide informed consent will be enrolled into the study and randomized in a double-blind manner at the study site. Subjects will be randomized to placebo control 2 mL; placebo control 4 mL; or active (73 mg or 146 mg) in a 1:1:4:4 ratio.

A randomization scheme will be used to program an Interactive Web-based Response System (IWRS). If considered eligible, subjects will be randomly assigned to a treatment group on Day 1 using this system. When a subject is randomized, the IWRS will assign a randomization number for each subject, corresponding to a specific treatment code. The randomization number will be automatically input into the eCRF by the system. The corresponding treatment code will only be accessible to the unblinded personnel.

For each drug distribution visit, the randomization number and the study treatment code assigned to a given subject, will then be used to select the appropriate bottle of blinded study drug for that subject for the corresponding visit.

The randomization scheme and corresponding treatment code will be kept strictly confidential, accessible only to authorized persons, until the time of unblinding. If a subject discontinues from the study, neither the subject identification number nor the allocated randomization code will be reused, and the subject will not be allowed to be re-randomized to the study.

### **8.2 Subject Informed Consent**

Written consent will be obtained from the subject prior to any study-specific procedure or investigation.

Information about the study will be given to the subject both verbally and in writing in a language (eg, English) that is understood by the subject. The written subject information will explain the objectives of the study and its potential risks and benefits. The subject should have adequate time to read the information and to ask the Investigator any questions. The Investigator must be satisfied that the subject has understood the information provided before written consent is obtained. If there is any doubt as to whether the subject has understood the written and verbal information, the subject should not enter the study.

If a subject agrees to participate, then he/she will be asked to sign and date an ICF, the original of which will be kept by the Investigator. A copy of the signed ICF will be given to the subject. A record should also be made in the notes that the subject voluntarily agreed to participate in the study and the original, signed ICF must be made available to the study monitor for inspection.

## **8.3 Study Visits**

### **8.3.1 *Scheduled Visits***

For each subject, a maximum of 10 scheduled visits will be performed. The procedures and assessments to be performed during each period/time point are indicated in the Schedule of Assessments. Further relevant details of the evaluations to be performed at each visit are described below.

#### **Screening Period (Day -45 to Day -28)**

- Written informed consent will be obtained.
- Subject eligibility will be determined based on IENFD score, medical history, physical examination, height and weight, review of entry criteria, 12-lead ECG, clinical laboratory tests (including serum pregnancy test for females), hepatitis/HIV screening, and drug/alcohol/urine screening.

#### **Baseline Period (Predose Day 1/Baseline)**

- On day 1, the subject will visit the clinical unit and will be evaluated to ensure that he/she meets entry criteria. The subject should arrive fasted (12 hours).
- On day 1, the subject will have the baseline assessments and safety laboratory evaluations performed as indicated in the Schedule of Assessments.
- Assessments for AEs will occur throughout the baseline period.

#### **Treatment Period (Day 1 through Week 24)**

- The subject will receive the investigational product and will be trained on how to apply the material on day 1.
- Blood (a single 2 mL sample) will be collected for PK trough levels, at weeks 2, 4, 8, 12, 16, 20, and 24.
- Pharmacodynamic and efficacy evaluations will be performed as indicated in the Schedule of Assessments.
- Blood for clinical laboratory tests will be drawn after an overnight fast (12 hours) at weeks 2, 4, 8, 12, 16, 20, and 24.
- Assessments for AEs and queries for concomitant medication usage will occur throughout the treatment period.

#### **Post-treatment Follow-up Visit (Week 26)**

- The subject will be assessed for AEs and queried for concomitant medication usage since previous visits.
- Symptom directed physical exam.

- Biopsy examination and suture removal, if necessary.

### **8.3.2    *Unscheduled Visits***

Should there be need for an unscheduled visit, (eg, to manage or follow up on unresolved AEs), the Investigator should use their judgment and perform an adequate evaluation of the subject. Vital signs, physical examination, and ECG findings should be performed as necessary and the data recorded in the Unscheduled Visit section of the eCRF.

## **8.4    General Restrictions**

### **8.4.1    *Fasting Treatment Periods***

On all visit days during which clinical laboratory samples will be obtained, subjects will have fasted for approximately 12 hours (overnight) before sample collection.

### **8.4.2    *Smoking***

Smoking is not prohibited during the trial. However, a stable nicotine intake regimen is required 3 months prior to participation in the trial and throughout the duration.

### **8.4.3    *Physical Exercise***

No change from prestudy exercise routine is requested.

### **8.4.4    *Contraceptive Measures***

The subject or their heterosexual partner (if applicable) should be surgically sterile (vasectomy, hysterectomy, bilateral tubal ligation [both tubes tied], or bilateral oophorectomy [both ovaries removed]). If not, and the female subject or partner is of childbearing potential (ie, could become pregnant), the subject must agree to use highly effective contraception during heterosexual intercourse throughout the study period and for 1 month following the last dose of the study drug.

#### **8.4.4.1    Acceptable Forms of Contraception**

A highly effective method of birth control is defined as those that result in a low failure rate (ie, less than 1% per year) when used consistently and correctly **When used individually, hormonal, barrier, or IUD methods alone are not acceptable.**

Examples of acceptable forms of highly effective contraception include the following:

- Established use of oral, injected, or implanted hormonal methods of contraception in combination with a barrier method(e.g, combined oral contraceptives, patch, vaginal ring, injectables, and implants).
- Placement of an IUD or intrauterine system in combination with a barrier method.

- Sterilized male partner (with the appropriate post-vasectomy documentation of the absence of sperm in the ejaculate) in combination with a barrier method.
- True abstinence: When this is in line with your preferred and usual lifestyle.

Examples of nonacceptable methods of contraception include:

- Barrier method alone (male condom, female condom, contraceptive sponge, cervical cap, diaphragm, etc.)
- Periodic abstinence (eg, calendar, ovulation, symptothermal, post-ovulation).
- Withdrawal.
- Spermicide.

However, if a form of highly effective method of birth control is not achievable, then a combination of at least two of the barrier methods listed above may be used (e.g. male condom with diaphragm, male condom with cervical cap, etc).

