#### Screening Period (Days -45 to -28)

Subjects will be screened for eligibility during a screening period that must be completed 28 days before baseline/day 1 (ie, the screening biopsy must be taken no later than day -28 in order to allow the screening biopsy to heal). During the screening period, all necessary assessments will be performed and subject eligibility for entry into the double-blind portion of the study will be verified. Subjects who do not qualify will be discontinued and considered screen failures. If during screening, a subject fails to meet any inclusion or exclusion criteria, then the Investigator is not required to complete the remaining screening activities. The following procedures will be performed during the screening period:

- Obtain signed informed consent from the subject before any study-specific procedures are performed
- Medical history review with the subject
- Demographic information collection
- Inclusion and exclusion criteria review
- Toronto Clinical Neuropathy Score
- Modified Toronto Clinical Neuropathy Score
- Sural nerve amplitude (accepted if  $> 1 \mu\text{V}$ )
- Skin Biopsy for IENFD (accepted if  $> 1$  and  $< 10$  IENF/mm)
- Quality of Life (Norfolk-QOL-DN)
- Quantitative thermal threshold (screening)
- Quantitative vibration perception (screening)

- Dermal Draize Score (screening)
- Prior and concomitant medications review
- Complete physical examination, including height and body weight (for body mass index [BMI] calculation)
- Supine and standing vital signs
- 12-lead ECG
- Serum pregnancy test (women of childbearing potential only)
- Clinical laboratory tests
- Serology for hepatitis B surface antigen, hepatitis C antibody, and human immunodeficiency virus (HIV) 1 and 2 antibody
- Urine drug screen and alcohol breathalyzer test
- AEs
- Verify that subject is physically able to inspect lower leg, upper and lower foot for wounds, infections, or other anomalies, and will be able to self-administer the investigational drug

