| 
* = It is acceptable to change the schedule of assessments in order to accommodate local and global health concerns and ensure patient safety due to Covid19.
 
a = The ET and EOS visits (week 24) will follow the same procedures.
 
b = Symptom directed physical examination.
 
c = Body weight and BMI calculation only. Height is taken at screening only.
 
d = Blood samples will be collected for serum chemistry and hematology, and urine will be collected for urinalysis (refer to section 7.2.2) at each visit. Subjects will be required to fast for at least 12 hours prior to collection.
 
e = For women of childbearing potential, a serum pregnancy test will be performed at screening and EOS/week 24. A urine pregnancy test will be performed at the Baseline visit.
 
f = Two standard 3-mm skin biopsies will be collected during the Screening visit from the distal leg or calf; approximately 10 cm above the malleolus and 3 cm to the posterior; and from the untreated area on the lateral thigh, approximately 25 cm below the iliac spine, approximately 5 cm below the level of the pubis and 8 cm to the posterior.
 
g = Prophylactic antibiotics may be administered to participants who, in the judgment of the Investigator, are considered to be at high risk for infection of the biopsy site.
 
h = Randomization will be prior to dose administration on day 1.
 
i = Investigational product will be administered by the subject by dispensing material from pump into palms of the hand and then spreading evenly over the calves (mid-calf sock-line), ankles and tops, and bottoms of feet.
 
j = Skin irritation (including dryness, redness, swelling, itching, burning/stinging) at the application site will be assessed using a Dermal Draize Scale prior to dosing on visit days.
 
k = Trough blood samples (1 sample at each specified visit) will be collected for pharmacokinetic analysis.
 
l = Two standard 3-mm skin biopsies will be collected during the EOS visit for early terminations or the week 24 visit. The biopsies will be collected at a distance of no less than 2 cm away and no further away than 3.5 cm from the baseline biopsy location.
 
m = The biopsy sites will be examined at the 26-week visit to monitor healing and remove sutures, if necessary. If the sutures are not suitable for removal, another visit for suture removal will be scheduled.
 
n = The visual analogue score will be collected weekly via a mobile phone application completed by the patient at the same time each week.
 |                |                |            |                |                  |                |                |                |                |                       |                 |

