### 6.2 Inclusion Criteria

Subjects must meet all of the following inclusion criteria to be eligible to participate in the study:

1. Diagnosis of T2DM (as defined by the 2013 Diabetes Canada guidelines).
2. Male and female patients in the age range of 18 to 75 years (inclusive).
3. Presence of definite diabetic neuropathy (as defined by the Toronto Consensus Guidelines) of at least 12 months duration in the lower extremities.
4. Provide written informed consent prior to entering the study or undergoing any study procedures.
5. Females should be either not of childbearing potential as a result of surgery or menopause (1 year after onset), or of childbearing potential and must be practicing a highly effective medically acceptable method of contraception (e.g. abstinence, or hormonal contraceptives (e.g. combined oral contraceptives, patch, vaginal ring, injectables, and implants); intrauterine device (IUD) or intrauterine system (IUS); or vasectomy (partner)) for at least 1 month before the screening visit and for 1 month after the last dose of study drug. If access or use of a highly effective medically acceptable method of contraception is not achievable, then a combination of barrier methods (e.g. male condom, female condom, cervical cap, diaphragm, contraceptive sponge) is acceptable (e.g. male condom with diaphragm, male condom with cervical cap). Eligible female subjects must also have a negative serum beta-human chorionic gonadotropin ( $\beta$ -hCG) at the screening visit.
6. Males must use an acceptable form of contraception (e.g. male condom with diaphragm, male condom with cervical cap, or male condom in association with spermicide)
7. Glycemic control has been optimized and has been stable for at least three months prior to randomization. Optimal glycemic control refers to the best possible diabetic control that an individual patient can attain with usual standards of care, which usually takes more than two months to establish.
8. Patients must have a screening IENF density range of no less than 1 IENF/mm and no more than 10 IENF/mm.
9. Participating subjects must be reliable, willing, and able to cooperate with all study procedures, including the following:
  - Return for study visits on the required dates

- Be physically able to inspect calves, tops of ankles, and soles of feet for wounds, infections, or other anomalies, and be able to self-administer the investigational drug to calves and feet.

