### 12.3 Pregnancy

Female subjects must be surgically sterile (hysterectomy, bilateral oophorectomy, or bilateral tubal ligation) **or** if a female subject is of childbearing potential, she must agree to use a medically acceptable, highly effective method of contraception during the study and for 1 month after the last dose of study drug to be eligible for participation in the study (see Inclusion Criteria, [section 6.2](#); and Contraceptive Measures). All female subjects must have a negative serum pregnancy test at screening and a negative urine pregnancy test at screening day and day 1 to be eligible for the study. A urine pregnancy test will also be performed at the end of the study at the post-treatment follow-up visit.

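### The contraception rules for entry contradict each other between sections 6.2 and 8.4.4.1, with smaller mismatches on pregnancy tests, sural amplitude and IENFD limits

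*Protocol*

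**What the plan says.** **Contraception.** Under inclusion criterion 5 (section 6.2), a woman of childbearing potential "must be practicing a highly effective medically acceptable method of contraception (e.g. abstinence, or hormonal contraceptives". The criterion then continues with an IUD or intrauterine system, or a vasectomised partner, joined by *or*. Section 8.4.4.1 says the opposite in bold for two of these: "When used individually, hormonal, barrier, or IUD methods alone are not acceptable". Its list of acceptable forms pairs hormonal methods, intrauterine methods and partner vasectomy each with a barrier. Section 8.4.4 asks for highly effective contraception only where neither the subject nor the partner is surgically sterile, and it counts vasectomy as sterility.

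**Pregnancy tests.** Section 12.3 requires all female subjects to have negative serum and urine tests at screening and a negative urine test on day 1 in order to be eligible. It adds: "A urine pregnancy test will also be performed at the end of the study at the post-treatment follow-up visit". Table 1 note e reads: "For women of childbearing potential, a serum pregnancy test will be performed at screening and EOS/week 24", with a urine test at baseline. Section 7.2.2 gives the same schedule as note e.

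**Sural amplitude.** The screening list in section 5.1 has "Sural nerve amplitude (accepted if" followed by a limit of more than 1 µV. Section 8.3.1 says: "Subject eligibility will be determined based on IENFD score, medical history, physical examination", and the rest of that list does not name sural testing.

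**IENFD.** Section 5.1 has "Skin Biopsy for IENFD (accepted if" followed by more than 1 and less than 10 IENF/mm. Inclusion criterion 8 reads: "Patients must have a screening IENF density range of no less than 1 IENF/mm and no more than 10 IENF/mm". Exclusion criterion 1 agrees with criterion 8.

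**The concern.** An entry rule should give the same answer wherever it is read. On contraception it does not. Section 8.4.4.1 cannot be set aside as advice on conduct after enrolment, because section 12.3 makes contraception a condition of eligibility and points to both section 6.2 and the contraceptive section.

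The study runs at several sites. Violation of an entry criterion is a ground for withdrawal (section 6.4, item 3), and the sponsor may require withdrawal of any subject who violates the protocol (section 8.5). Where two sections disagree, whether a subject is a violator depends on the section consulted. The primary objective is safety, and every pregnancy with possible exposure must be followed to term (section 12.3.1), so contraception and pregnancy testing are where a single clear rule matters most. These are conflicts inside the protocol about who may enter, and a statistical analysis plan would not settle them.

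**Working it through.** No figure is involved, so the check is to apply each section to the same example subject.

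| Example subject | Accepted under | Not accepted under |
|---|---|---|
| Woman using one hormonal method, no barrier | 6.2, criterion 5 | 8.4.4.1 (bold sentence) |
| Woman using an IUD, no barrier | 6.2, criterion 5 | 8.4.4.1 (bold sentence) |
| Woman with vasectomised partner, no barrier | 6.2, criterion 5; 8.4.4 | Not among the acceptable forms in 8.4.4.1 |
| Woman of childbearing potential, negative serum test at screening and negative urine test on day 1 | 6.2, 6.3, Table 1, 7.2.2 | 12.3 (no screening urine test) |
| Sural amplitude of 1 µV or less | Nothing in 6.2 or 6.3 bars entry | 5.1 |
| IENFD exactly 1 or exactly 10 IENF/mm | 6.2, criterion 8; 6.3, criterion 1 | 5.1 (screening and baseline) |

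**Contraception.** The sections agree on abstinence, and on two barrier methods where a highly effective method cannot be achieved. They disagree on single hormonal and single intrauterine methods. For these the bold sentence is categorical, so it does not help that the lists below it are headed as examples. The vasectomy conflict is a little softer: 8.4.4.1 lists it only with a barrier but does not name it in the bold sentence.

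**Pregnancy tests.** The sections agree on a serum test at screening and a urine test at baseline in women of childbearing potential. They differ in three ways:

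1. Section 12.3 adds a urine test at screening.
2. Section 12.3 applies the entry tests to all females. Table 1, 7.2.2 and the screening list in 5.1 restrict them to women of childbearing potential; the baseline bullet in 5.1 carries no restriction.
3. Section 12.3 adds a urine test at follow-up. Table 1 has a serum test at week 24 and nothing at week 26, and the follow-up lists in 5.1 and 8.3.1 name no pregnancy test.

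Only the first two bear on entry. The third is a schedule conflict.

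**Sural amplitude.** None of the 13 inclusion or 35 exclusion criteria contains the limit. Section 7.1.2 records an amplitude for each leg, while 5.1 names no leg, so a subject with one leg above 1 µV and the other at or below it is undefined even under 5.1.

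**IENFD.** Strict and inclusive limits give the same answer at every value except exactly 1 and exactly 10. Section 7.1.1 obtains the density as a fibre count divided by a measured length, so exact boundary values should be rare. The protocol gives no frequency.

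**The case against.** The fairest objection is that these items are very unequal and that the protocol limits the damage. Much of that stands.

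- The sural limit is one threshold against silence, not two rival limits. A site that applied the whole document would have one rule. What remains is that the threshold is missing from the formal criteria and names no leg.
- Every section requires contraception and a negative screening pregnancy test in women of childbearing potential. The pregnancy-test conflict concerns an extra test and who is tested, not opposing thresholds.
- Inclusion criterion 12 sends eligibility questions to the medical monitor, who is also involved in violations (6.4) and deviations (8.5). This limits the effect but does not correct the text.

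Three stronger readings are tempting, and the document does not support them.

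- A reader might infer that sites will enrol different populations. The protocol gives no number of women using a single method, no distribution of sural amplitude, and no account of how sites screen. The age range is 18 to 75, and criterion 5 exempts postmenopausal women, so the affected group could be small.
- A reader might weigh one wrongly entered subject as 1/12 ≈ 8% of control. That holds only if the subject is on placebo. Of the 60 planned subjects, 24 + 24 = 48 (80%) go to active arms, where one subject is 1/24 ≈ 4%. Eligibility is settled before randomization, so the ambiguity favours no arm. The per-protocol definition in 13.1.2 rests on compliance and completed visits, not on entry violations.
- A reader might add section 7.2.7, which says BMI is used to confirm eligibility. No BMI limit exists anywhere, so nobody's eligibility can differ. It is a stray phrase.

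**Conclusion.** The point holds, with contraception as its core. For a woman of childbearing potential using a single hormonal or intrauterine method, sections 6.2 and 8.4.4.1 give opposite answers, and section 12.3 makes both relevant to eligibility. Partner vasectomy is treated in two ways. In second place come the screening urine test, required for entry by 12.3 but not scheduled, together with the unscheduled follow-up test, and the sural threshold that appears only in 5.1. The IENFD boundary is an editorial matter.

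The size cannot be put as a number of subjects, because the document gives no frequencies. No sample size, analysis set or test is affected. The consequence is inconsistent enrolment and uncertainty over what counts as an entry violation. The conclusion rests on the current text of the sections named and takes no view on which clinical rule is right.

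**What to change.** The sponsor should reconcile these passages so that each rule is stated once, in 6.2 or 6.3, and have 5.1, 8.3.1, 8.4.4, 8.4.4.1 and 12.3 refer to it:

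- One contraception rule, covering single hormonal methods, intrauterine methods and partner vasectomy.
- One pregnancy-test schedule, held in Table 1, saying who is tested, with which test and at which visits. Section 7.2.2 should refer to it.
- One IENFD limit, either strict or inclusive at both ends.
- The sural threshold either listed in 6.2 with the leg it applies to, or the acceptance wording removed from 5.1.

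The clinical content of each rule is the sponsor's choice. The cost is amendment wording and a memo to sites. The planned 60 subjects and the analyses stay as they are.
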